## Abstract

**Background:**

Breast cancer therapy improved significantly, allowing for different surgical approaches for the same disease stage, therefore offering patients different aesthetic outcomes with similar locoregional control. The purpose of the CINDERELLA trial is to evaluate an artificial-intelligence (AI) cloud-based platform (CINDERELLA platform) vs the standard approach for patient education prior to therapy.

**Methods:**

A prospective randomized international multicentre trial comparing two methods for patient education prior to therapy. After institutional ethics approval and a written informed consent, patients planned for locoregional treatment will be randomized to the intervention (CINDERELLA platform) or controls. The patients in the intervention arm will use the newly designed web-application (CINDERELLA platform, CINDERELLA APProach) to access the information related to surgery and/or radiotherapy. Using an AI system, the platform will provide the patient with a picture of her own aesthetic outcome resulting from the surgical procedure she chooses, and an objective evaluation of this aesthetic outcome (e.g., good/fair). The control group will have access to the standard approach. The primary objectives of the trial will be i) to examine the differences between the treatment arms with regards to patients’ pre-treatment expectations and the final aesthetic outcomes and ii) in the experimental arm only, the agreement of the pre-treatment AI-evaluation (output) and patient’s post-therapy self-evaluation.

**Discussion:**

The project aims to develop an easy-to-use cost-effective AI-powered tool that improves shared decision-making processes. We assume that the CINDERELLA APProach will lead to higher satisfaction, better psychosocial status, and wellbeing of breast cancer patients, and reduce the need for additional surgeries to improve aesthetic outcome.

## Introduction

Shared decision-making is a key component of patient-centred health care. This is a process in which the care team, particularly the treating physician and the patient, work together to make decisions on the treatment plans based on clinical evidence and the individual clinical case, while balancing risks and expected outcomes with patient preferences, expectations, moral beliefs, and values [1]. The physician’s role is to clearly communicate the pros and cons of each approach, the risks, benefits and consequences of each approach, in a language and manner that the patient can easily comprehend. This approach empowers patients to make informed decisions about the proposed options based on a broad understanding of each treatment offered. However, providing information is often not sufficient to help the patient achieve full appreciation of what is at stake and give his/her informed consent [1].

Newly diagnosed breast cancer patients are put in the position of having to make difficult decisions several times during their treatment journey [2]. Current treatment approaches are multimodal, including surgery, systemic therapy, and radiation [3]. Patients might be given a choice for sequencing therapy (e.g., systemic therapy before or after surgery) that may influence the type of locoregional therapy (e.g., from mastectomy to breast conservation). In each modality, the patients might be offered different choices of therapy (e.g., different systemic agents, mastectomy or oncoplastic surgery), based on their personal risk factors (e.g., age, comorbidities) and disease-related factors (e.g., stage, molecular subtype) and physician preference. Surgical management is no longer the one-size-fits-all mutilating procedure of radical (even if modified) mastectomy that governed breast surgery for almost 100 years, but evolved to offer better aesthetic outcomes, improved quality of life (QoL) and psychological well-being of patients [4, 5]. For a given breast cancer stage, the patient might be offered different types of breast and lymphatic surgeries and various radiation protocols, with similar oncological outcomes, which might be challenging to explain to the patient [2, 5]. Based on the patient’s individual risks/factors (e.g., smoking, body mass index), location of the primary tumour, surgical procedure and surgeon’s expertise, and whether radiation was applied, the aesthetic outcomes might vary significantly between patients undergoing the same treatment [6].

Current practice for deciding on locoregional therapy and shared decisions varies between centres and may include pictures, drawings, brochures, referral to the centre’s website, and a meeting with a variety of staff members, but it is not uniform and does not consider all the patient’s individual factors. In addition, breast cancer patients who refer to social media or unsupervised websites for information may be subjected to misinformation [7]. Social media can be particularly persuasive as it is used daily to access a wide range of information including medical information. Moreover, the information has an emphasis on visual content and personal experiences [7]. Thus, this misinformation might challenge the shared decision process of the patient and her caregiver.

Even though locoregional therapy has significantly improved, one third of the patients might have poor aesthetic outcomes, which in turn may also affect patient’s well-being [8]. Furthermore, the different treatment options are based on knowledge of oncological outcomes and there are no tools currently available for everyday clinical practice use to help predict or evaluate patient-centred outcomes, in particular aesthetic outcomes. Quality indicators have not been developed neither for the aesthetic evaluation of locoregional breast cancer treatments, nor for measuring patient’s satisfaction and matching of expectations [9]. Patients might value outcomes differently when comparing them with what they expected [10]. This helps explain why this important aspect of breast cancer care is poorly standardized and is often out of scope when auditing procedures. This means that in many cases of “shared decision process” for locoregional therapies in breast cancer, both the caregiver and the patient are left unguided and cannot fully anticipate the impact of each therapy on the aesthetic outcome, patient’s body image, well-being, and QoL. Moreover, the process might be challenged by prejudice due to misinformation from unsupervised sources of information [1, 7].

The CINDERELLA project is based on collaboration between leading breast cancer clinical centres and health industry partners INESC TEC & CANKADO to create an easy-to-use, cost-effective web-based tool for patients and their families to improve the communication with health providers and assist the informed consent process prior to locoregional therapy for breast cancer. As part of the project, the CINDERELLA trial is planned as a prospective multicentre randomized controlled trial [Clinical Trials.gov Identifier 05196269] to evaluate conventional methods for patient education prior to therapy versus an artificial-intelligence cloud-based healthcare platform (CINDERELLA APProach) in breast cancer patients planned for locoregional treatment. The project is supported by the European Union [EU grant HORIZON-HLTH-2021-DISEASE-04-04. HORIZON-RIA. Proposal number 101057389]. The interventional arm will have access to a newly design web-platform (CINDERELLA platform, CINDERELLA APProach), that provides information about the locoregional therapy and the possible aesthetic outcomes (visual with a scale) according to the different type of surgeries the patient was offered. The types of surgeries offered, and patient’s choice will be recorded for both groups. Patients’ expectation and satisfaction with the outcomes will be recorded. We anticipate that the CINDERELLA APProach will improve patient’s expectations and result in greater satisfaction with locoregional therapy outcomes compared to methods currently used in clinical practice.

## Methods

Prospective randomized international multicentre parallel group trial conducted in 5 clinical centres, each attaining an institutional ethics approval. All patients will need to sign a written informed consent form. Randomization will be performed centrally, 1:1 to control arm (conventional current clinical practice for patient education prior to therapy) or intervention arm. Randomization will follow the minimization method proposed by Pocock and Simon [11, 12], a covariate-adaptive randomization procedure that achieves balance within covariate margins. The randomization procedure requires randomization lists of two types: (1) 50:50 lists, with blocks of size two will be used to assign the patients when balance between groups is attained during the randomization process. (2) Unbalanced 20:80 and 80:20 randomization lists in blocks of size five will be used to assign the patients otherwise (Fig 1).

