**Fig 1 pone.0289365.g001:**
[figure not shown]
Rationale of the randomization method.

The intervention arm will have access to the CINDERELLA platform which entails the information related to surgery and/or radiotherapy. Upon patient’s request, the platform will provide the patient with a matched picture as an example of her own aesthetic outcome according to the surgical procedure she chooses, and an objective evaluation of this aesthetic outcome (e.g., good/fair). The trial will not interfere with the type of locoregional therapy offered to the patient, or any treatment, but will evaluate the CINDERELLA approach and standard approach in terms of achieving an optimized shared decision making.

In total, considering both primary objectives (i) to evaluate the differences between the arms in patient’s agreement of expectations and aesthetic outcome and (ii) in the experimental arm only, the agreement of the AI-evaluation and patient’s post-therapy self-evaluation, it is estimated that a minimum of 515 patients will be enrolled in each arm of the study, based on recent information (frequency and dropout) from the clinical centres. The trial objectives are summarized in Table 1. Sample size was calculated in a two-step simulation-based approach using information from a previous study and expert clinical opinion for the 1^st^ and the 2^nd^ primary objectives, respectively. The simulation studies considered the use of weighted Cohen’s k to calculate the level agreement with a precision of 0.1 and a confidence level of 95% [13, 14]. The proposed sample size was obtained after a 40% correction to account for potential dropout.

**Table 1 pone.0289365.t001:** CINDERELLA trial–objectives.

TRIAL OBJECTIVES

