**Primary objectives:** 1. To evaluate the difference between both arms of the trial, regarding the match of expectations about the aesthetic outcome before and after treatment. 2. Experimental arm only, the agreement of the pre-treatment AI-evaluation (output) and patient’s post-therapy self-evaluation. **Secondary objectives:** 1. To evaluate the difference, between both arms of the trial, in patient’s body image satisfaction after surgery. 2. To evaluate the difference between both arms of the trial, in health resource consumption (time spent in hospital, number of appointments, duration until treatment additional care sought by patients). 3. To evaluate the difference, between both arms of the trial, in patient’s satisfaction with their professional life. 4. To evaluate the difference between both arms of the trial, in patient’s satisfaction with their sexual life. 5. To evaluate the difference, between both arms of the trial, in patient’s satisfaction with their general health-related quality of life.

Stratification will be considered to balance potential confounding factors that might influence aesthetic outcomes, i.e., type of surgery (conservative, mastectomy), patient age (<50, 50+) and radiotherapy (yes, no) (see flowchart in Fig 1). This randomization procedure was implemented and simulated using R, a free software environment for statistical computing and graphics (R Core Team, 2022 ®), following the minimization method proposed by Pocock and Simon [11, 12], a covariate-adaptive randomization procedure that achieves balance within covariate margins. The randomization was designed to be implemented in each of the centres and then, integrate the trial as a whole.

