Investigational arm-only: prior to deciding on locoregional therapy the patient will be given access to the CINDERELLA platform. The platform will contain clinical information as mentioned above. The patient breasts will be photographed prior to therapy by the research team. The BreLO AI (version 1.0) will match the patient biometrics and images with a similar case existent in the BreLO repository and already classified by the BCCT.core (version 4.0) into excellent, good, fair and poor. The patient can then visualize the results presented as synthetized images of her own body. BreLO AI will include an automatic image quality assessment module; if the images of the patient are below a quality standard, the matching will fail with an error message for the user.

All trial information will be fed into the platform to improve the AI-system for performing biomatching. To promote participant retention and complete follow-up, an intense training of nurses in each site as well as continuous proactive follow-up will be ensured. If participants discontinue or deviate from intervention, we will document that event but not obtain any special outcome data.

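### Fixed blocks of two and five inside the minimisation leave about 44–45% of allocations with no random element; independent draws at the same probabilities would remove this at no cost in balance

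*Protocol article*

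**What the plan says.** The Methods section of the protocol article describes Pocock–Simon minimisation on three two-level factors (type of surgery, age and radiotherapy), with allocations read from two kinds of list. For the balanced state: "50:50 lists, with blocks of size two will be used to assign the patients when balance between groups is attained". For every other state: "Unbalanced 20:80 and 80:20 randomization lists in blocks of size five will be used to assign the patients otherwise". Both block sizes are fixed and stated in print.

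On where the procedure runs, the same section says two things. At its start: "Randomization will be performed centrally, 1:1 to control arm". After Table 1: "The randomization was designed to be implemented in each of the centres and then, integrate the trial as a whole". The trial is "conducted in 5 clinical centres", and centre is not named among the balancing factors.

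On visibility of the arm, the investigational-arm paragraph says that "prior to deciding on locoregional therapy the patient will be given access to the CINDERELLA platform". Controls receive usual patient education. No masking is described. The first primary objective (Table 1) concerns whether a woman's expectations about the aesthetic outcome are matched, which rests on her own answers.

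**The concern.** Minimisation is close to deterministic by construction. It needs a random element so that nobody can be sure of the next allocation. A biased coin provides this for every patient. A short permuted block provides it only for the early entries: the second entry of a block of two is always forced, and in a 4:1 block of five everything after the single minority entry is forced.

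The stake is selection at entry. The arm becomes known to staff as soon as it is given, so past allocations are on view even if the lists are held centrally. Eligibility also leaves room for judgement, for example on the ability to use a web application. Someone who foresees the platform arm could, without intending it, approach or defer patients differently. With a self-reported primary outcome, selection on unrecorded traits may escape covariate adjustment.

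**Working it through.** The article gives no predictability figure, so there is none to reproduce.

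**Inputs from the article (Methods).** Block of 2 at 1:1 when balanced; block of 5 at 4:1 or 1:4 otherwise; three binary factors; 5 centres; and "a minimum of 515 patients will be enrolled in each arm of the study", that is 2 × 515 = 1030 women, or 1030/5 = 206 per centre if recruitment is even (an assumption).

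**Inputs assumed.** Factor prevalences are not given. The ranges tried were 0.5/0.5/0.5, 0.3/0.3/0.8, and 65% conservative surgery with 40% under 50 and radiotherapy in 95% or 30% by surgery type. The imbalance measure is not in the visible text either; the sum of absolute marginal differences and the signed sum were both tried.

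**Step 1. Forced draws, exact.** A draw is forced when all remaining entries of the open block are the same arm.
- Block of 2: 1 of 2 = 50%.
- Block of 5 at 4:1: the minority entry is equally likely in each position, which leaves 4, 3, 2, 1 or 1 forced draws. The mean is (4+3+2+1+1)/5 = 2.2 of 5 = 44%.

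Over completed blocks, any mix of lists lies between 44% and 50%.

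**Step 2. Best guess, exact, for someone who knows the list state.**
- Block of 2: (0.5 + 1)/2 = 75%.
- Block of 5: (4 × 0.8 + 1)/5 = 84%.
- Independent draws: 50% when tied, 80% otherwise.

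**Step 3. Mix of the two lists.** With margins and lists per centre, simulation puts 14–22% of patients on the 50:50 list. Taking 21%:
- forced: 0.21 × 50% + 0.79 × 44% = 45.3%;
- best guess with lists: 0.21 × 75% + 0.79 × 84% = 82.1%;
- best guess with independent draws: 0.21 × 50% + 0.79 × 80% = 73.7%.

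Simulation gives 44.4–44.9% forced, 82–83% and 74–76%. It falls slightly below the hand figure for forced draws because some blocks end unfinished. The same effect is larger if each centre-by-stratum cell has its own lists, where 40–41% are forced. Prevalences and imbalance measure hardly move these figures.

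**Step 4. What one centre could foresee from its own log.** The forced share stays near 45% in each case below, but the site's success does not.

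| Arrangement | Correct guesses by a site reconstructing the lists |
|---|---|
| Margins and lists per centre, balance rule known | 82% |
| Margins and lists per centre, wrong balance rule assumed | 68–72% |
| Margins per centre, lists shared | 69–70% |
| Margins and lists shared | about 51% |

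In the second and third rows, reconstruction does no better than the 74% reached with independent draws by always guessing the favoured arm. An observer who tracks only arm totals reaches 65% with lists and 64% with independent draws.

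**Step 5. Balance.** For 206 women per centre, the mean arm difference is 0.8–0.9 patients with lists and 1.1 with independent draws. The largest factor-level difference is 2.5 against 2.4.

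**The case against.** A reader might infer that about 45% of allocations can be predicted by any centre from its own records. The article does not support that. It says randomisation is central, and the sentence about implementation in each centre goes on to speak of integrating the trial as a whole, which may mean shared lists or margins. Fig 1, which might settle this, is not available here. The visible text also does not define balance: neither the imbalance measure nor any weights are given, so a site could not be sure which list produced a past allocation. A persistent observer might learn the rule from contradictions, but that takes a full log of factors and arms and a running reconstruction of three interleaved lists. Nothing suggests anyone would do this.

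It is also fair to say that most of the predictability is the 0.8 minimisation itself, which the fix keeps: the best-informed observer loses about 8 points (82% to 74%), not more. And it would be too strong to say that analysis cannot repair the harm, because the Statistical analysis section plans models adjusted for patient and disease characteristics. Only selection on traits outside those models would remain.

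These points limit the size of the problem. They do not give a reason to keep the blocks. The forced share follows from the printed block sizes under every arrangement, and the blocks bring no material gain in balance.

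**Conclusion.** The concern holds in a conditional form. As a property of the lists, about 44–45% of draws are fully determined (40–41% with lists per centre-by-stratum cell). Whether a site could use this depends on three conditions together: lists and margins both kept per centre, the balance rule known to staff, and the factors and arms of all earlier patients logged. Under all three, best-guess success is about 82% against about 74% with independent draws. If any one fails, the advantage is much smaller or absent.

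That the trial is open is inferred from the nature of the intervention and the absence of any described masking. The finding shows an avoidable vulnerability in a trial with a self-reported primary outcome. It does not show that allocation has been or will be subverted, or that the results will be biased. Bias from unmasked self-report is a separate matter that this change would not touch.

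**What to change.** Replace the permuted lists with an independent random draw for each patient at the plan's own probabilities: 0.5 when the minimisation score is tied, and 0.8 for the under-represented arm otherwise. Leave the factors, the 1:1 ratio and the sample size as they are. In the same place, state whether margins are kept per centre or trial-wide.

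The cost is a small change to the R randomisation code and a sentence or two in the protocol. Forced draws fall to 0%, balance is essentially unchanged, and no extra patients are needed.

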**Fig 1 pone.0289365.g001:**
[figure not shown]
Rationale of the randomization method.

The intervention arm will have access to the CINDERELLA platform which entails the information related to surgery and/or radiotherapy. Upon patient’s request, the platform will provide the patient with a matched picture as an example of her own aesthetic outcome according to the surgical procedure she chooses, and an objective evaluation of this aesthetic outcome (e.g., good/fair). The trial will not interfere with the type of locoregional therapy offered to the patient, or any treatment, but will evaluate the CINDERELLA approach and standard approach in terms of achieving an optimized shared decision making.

In total, considering both primary objectives (i) to evaluate the differences between the arms in patient’s agreement of expectations and aesthetic outcome and (ii) in the experimental arm only, the agreement of the AI-evaluation and patient’s post-therapy self-evaluation, it is estimated that a minimum of 515 patients will be enrolled in each arm of the study, based on recent information (frequency and dropout) from the clinical centres. The trial objectives are summarized in Table 1. Sample size was calculated in a two-step simulation-based approach using information from a previous study and expert clinical opinion for the 1^st^ and the 2^nd^ primary objectives, respectively. The simulation studies considered the use of weighted Cohen’s k to calculate the level agreement with a precision of 0.1 and a confidence level of 95% [13, 14]. The proposed sample size was obtained after a 40% correction to account for potential dropout.

**Table 1 pone.0289365.t001:** CINDERELLA trial–objectives.

TRIAL OBJECTIVES
**Primary objectives:** 1. To evaluate the difference between both arms of the trial, regarding the match of expectations about the aesthetic outcome before and after treatment. 2. Experimental arm only, the agreement of the pre-treatment AI-evaluation (output) and patient’s post-therapy self-evaluation. **Secondary objectives:** 1. To evaluate the difference, between both arms of the trial, in patient’s body image satisfaction after surgery. 2. To evaluate the difference between both arms of the trial, in health resource consumption (time spent in hospital, number of appointments, duration until treatment additional care sought by patients). 3. To evaluate the difference, between both arms of the trial, in patient’s satisfaction with their professional life. 4. To evaluate the difference between both arms of the trial, in patient’s satisfaction with their sexual life. 5. To evaluate the difference, between both arms of the trial, in patient’s satisfaction with their general health-related quality of life.

Stratification will be considered to balance potential confounding factors that might influence aesthetic outcomes, i.e., type of surgery (conservative, mastectomy), patient age (<50, 50+) and radiotherapy (yes, no) (see flowchart in Fig 1). This randomization procedure was implemented and simulated using R, a free software environment for statistical computing and graphics (R Core Team, 2022 ®), following the minimization method proposed by Pocock and Simon [11, 12], a covariate-adaptive randomization procedure that achieves balance within covariate margins. The randomization was designed to be implemented in each of the centres and then, integrate the trial as a whole.

Eligibility criteria include: Female aged more than 18 years old; written informed consent; primary breast cancer in situ or invasive without evidence of systemic disease (non-Stage IV or locally advanced non-operable breast cancer); ECOG performance status 0 or 1; Uni or Bilateral breast surgery even if prophylactic in one side; Ability to use a web-based app autonomously or with home-based support. Exclusion criteria include: Mastectomy without reconstruction; pregnancy or lactation; Previous radiation to breast/chest (e.g., lymphoma); previous ipsilateral breast surgery due to malignant disease; other neoplasm in the last 5 years (excluding basal cell carcinoma of the skin and adequately treated carcinoma in situ of the cervix); severe skin disease that will contra-indicate the use of radiotherapy; previous breast prophylactic surgery; uncontrolled psychiatric disorder.

After randomization the patient will either follow the investigational arm with the CINDERELLA APProach vs. a conventional approach (control arm). For both study arms, patient’s breasts will be photographed (without identifiers) prior to any intervention. The patients will fill in an expectations questionnaire, resource consumption survey and patient-reported outcome measures (PROMs): EQ-5D-5L, EORTC QLQ C-30 and EORTC BR-23/EORTC QLQ BR-45, Harris Scale, and BREAST Q ICHOM. Questionnaires and photographs will be repeated after healing is completed, six months and one year after the end of treatment (surgery or radiotherapy if radiotherapy was done). Data manager will evaluate that all collected data and questionnaires are completed properly at the time of submission by the centres, to reduce the possibility of missing information and non-compliance with the protocol.

Investigational arm-only: prior to deciding on locoregional therapy the patient will be given access to the CINDERELLA platform. The platform will contain clinical information as mentioned above. The patient breasts will be photographed prior to therapy by the research team. The BreLO AI (version 1.0) will match the patient biometrics and images with a similar case existent in the BreLO repository and already classified by the BCCT.core (version 4.0) into excellent, good, fair and poor. The patient can then visualize the results presented as synthetized images of her own body. BreLO AI will include an automatic image quality assessment module; if the images of the patient are below a quality standard, the matching will fail with an error message for the user.

All trial information will be fed into the platform to improve the AI-system for performing biomatching. To promote participant retention and complete follow-up, an intense training of nurses in each site as well as continuous proactive follow-up will be ensured. If participants discontinue or deviate from intervention, we will document that event but not obtain any special outcome data.

